### Control group

Subjects in the control groups will not receive acupuncture treatments. They will receive conventional TH treatments only. Control group participants will then be assessed neurologically at each follow-up visit.

### Dropout criteria

Participants who meet any of the following criteria will be removed from the study: (1) study group subjects who miss more than three sessions (out of a total of 36) of acupuncture; (2) patients who withdraw their consent; (3) patients who experience severe adverse events making their further inclusion in the trial unsustainable; (4) patients whose neurological condition deteriorates making it difficult for them to continue participating in the trial; (5) patients who experience decompensation related to accompanying and/or additional diseases; or (6) patients whose further participation in the trial is felt to be impossible as determined by the principal investigator.

### Outcome measures

#### Primary outcome measure

The primary outcome measure will be NIHSS score, a measure of neurological status, at the end of treatment, at 30 days after TH, and at 90 days after TH. NIHSS is used to describe neurological deficits in stroke patients, and it strongly predicts the likelihood of a patient’s recovery after stroke. The NIHSS is comprised of 11 test items including level of consciousness, gaze, visual field defects, facial palsy, upper extremity motor, lower extremity motor, limb ataxia, sensory ability, language, dysphagia, and neglect. Total score ranges from 0 to 42, with scores above 25 indicating very severe neurological impairment, scores of 5 to 24 indicating moderately severe to severe impairment, and scores below 5 indicating mild impairment.

#### Secondary outcome measures

Secondary outcome measures are as follows:Poor outcome, defined as death or major disability, is defined as a score of 3 to 6 on the modified Rankin scale at 90 days after onset of TH. Scores on the modified Rankin scale range from 0 to 6, with a score of zero indicating no symptoms; a score of five indicating severe disability, confinement to bed, or incontinence; and a score of six indicating death.The rate of surgery at 30 days is defined as the incidence of neurological deterioration requiring surgical intervention.The Glasgow Outcome Scale (GOS) at 90 days after onset of TH is a measure of long-term outcome and includes five grades: 5, good recovery; 4, moderate disability; 3, severe disability; 2, persistent vegetative state; and 1, death.The Barthel activities of daily living (ADL) index and the Rivermead Mobility Index will be performed on each patient at the end of treatment, at 30 days after TH, and at 90 days after TH.Patients with left thalamic hemorrhages will also be evaluated with several language tests including the Boston Naming Test, the Boston Diagnostic Aphasia Exam, the Western Aphasia Battery, and the Mount Wilga High Level Language Screening Test at the end of treatment, at 30 days after TH, and at 90 days after TH.Patients with right thalamic hemorrhages will also be evaluated for visual neglect with the Behavioral In-attention Test (BIT) at the end of treatment, at 30 days after TH, and at 90 days after TH.

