### Intervention

Participants in both groups will receive conventional Western medical treatments as recommended by the guidelines for the management of spontaneous intracerebral hemorrhage including blood pressure management, ICP monitoring, appropriate prophylaxis, and surgical treatment as necessary for life-threatening hemorrhages [2]. In addition to conventional treatment, patients in the study group will receive 36 sessions (once a day, 6 days a week for 6 weeks) of acupuncture.

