### Acupuncture

Acupuncture treatment will be started within 72 h after TH onset, and applied once a day, 6 days a week for 6 weeks (a total of 36 sessions). The sessions will be performed by an experienced acupuncture doctor with over 10 years of working experience and 7 years of acupuncture training. This doctor will also receive training prior to the start of the trial. The acupuncture protocol was designed by a Sichuan University Huaxi Hospital professor with more than 25 years of practical experience, in accordance with guidelines from published papers and clinical experience. It will follow the Standards for Reporting Interventions in Clinical Trials for Acupuncture 2010 checklist, as shown in Table 1. Acupuncture points are identified by the point location method as described by the World Health Organization (WHO standard) [33].

**Table 1 Tab1:** Acupoints to be used in the study

Acupoint	Location	Major indication and function
MS 5 (Dingzhonxian)	At the top of the head, along the middle line of the head, connecting DU 20 to DU 21.	Prolapse, sacral and lumbar problems, paralysis, cortical polyuria, gastroptosis, hyperostosis, hypertension
MS 6 (Dingnieqianxiexian)	1 cun anterior from DU 20 to GB 6.	Treats motor function disorders
MS 7 (Dingniehouxiexian)	1 cun posterior to MS6, from DU 20 to GB 7.	Treats sensory function disorders
LI15 (Jian Yu)	On the shoulder girdle, in the depression between the anterior end of the lateral border of the acromion and the greater tubercle of the humerus.	Shoulder pain, paralysis
LI11 (Qu Chi)	On the lateral aspect of the elbow, at the midpoint of the line connecting LU5 with the lateral epicondyle of the humerus.	Upper extremity palsies, relaxes and strengthens tendons
SJ5 (Wai Guan)	On the posterior aspect of the forearm, at the midpoint of the interosseous space between the radius and the ulna, 2 B-cun proximal to the dorsal wrist crease.	Tinnitus, paralysis of the arms, upper extremity pain;
LI4 (He Gu)	On the dorsum of the hand, in the depression radial and proximal to the second metacarpophalangeal joint.	Spasm in the fingers
ST34 (Liang Qiu)	On the anterolateral aspect of the thigh, between the vastus lateralis muscle and the lateral border of the rectus femoris tendon, 2 B-cun superior to the base of the patella.	Gastrospasm, leg muscle atrophy

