### Sample size calculation

Using the variable NIHSS score, the primary outcome measure of the study, PS Power and Sample Size software (version 3.0) was used to determine an appropriate sample size for the study. In a previous study, NIHSS scores in each subject group exhibited a normal distribution with a standard deviation of 4.2 points [11]. This assumes a difference of 2.3 points between the groups, as shown in a previous study on moderate TH. A sample size of 488 provides 80% power (α = 0.05) to detect a beneficial effect of early acupuncture therapy on the primary outcome, assuming a 10% non-adherence to treatment and a 3% loss to follow-up.

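### Removing patients from the study for deterioration, or (acupuncture arm only) for more than three missed sessions, can lose 30-day surgery events unequally between arms

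*Protocol article*

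**What the plan says.** All references are to the protocol article.

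- **Outcome** (Secondary outcome measures): "The rate of surgery at 30 days is defined as the incidence of neurological deterioration requiring surgical intervention". The Abstract calls the same outcome need for surgery, which agrees with this definition.
- **Consequence of a dropout criterion** (Dropout criteria): "Participants who meet any of the following criteria will be removed from the study".
- **Criterion (1)**, acupuncture arm only: "study group subjects who miss more than three sessions (out of a total of 36) of acupuncture".
- **Criterion (4)**, both arms: "patients whose neurological condition deteriorates making it difficult for them to continue participating in the trial".
- **Treatment schedule** (Intervention; Acupuncture): "36 sessions (once a day, 6 days a week for 6 weeks) of acupuncture", and "Acupuncture treatment will be started within 72 h after TH onset".
- **Surgery** (Intervention) is part of conventional care in both arms: "surgical treatment as necessary for life-threatening hemorrhages".
- **Sample size calculation** makes one allowance for both kinds of attrition, "assuming a 10% non-adherence to treatment and a 3% loss to follow-up".

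Controls receive no acupuncture (Control group), so they have no sessions to miss.

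**The concern.** An outcome that counts deterioration leading to surgery should not be combined with a rule that takes deteriorating patients out of the study. Criterion (4) is worded in nearly the same terms as the event. Criterion (1) adds a second route that exists in one arm only: a patient who deteriorates or is operated on may well miss several daily sessions, and in the acupuncture arm that alone leads to removal. A control patient with the same course has no equivalent rule.

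At stake is the direction of any error. Events lost through criterion (1) are lost from the acupuncture arm, so its surgery rate would look lower without any true effect. The problem lies in a rule the article states. It does not rest on the article's silence about an analysis set, which may be covered in a document not shown.

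**Working it through.** **1. How easily criterion (1) is met.** More than three missed means four or more, and 4/36 = 11% of the course. With six treatment days and one rest day a week, four consecutive missed sessions span 4 calendar days, or 5 if the rest day falls among them.

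**2. Overlap with the 30-day window.** Acupuncture starts between day 0 and day 3 after onset.
- Start on day 0: 31 days through day 30, with 4 or 5 rest days, gives 26 or 27 sessions.
- Start on day 3: 28 days with 4 rest days gives 24 sessions.

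So 24 to 27 sessions fall by day 30, and 36 − 27 = 9 to 36 − 24 = 12 come later. Criterion (1) can therefore be met before or after an operation at any point in the window.

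**3. Two ways an event can be lost.**
- *Removal before the operation.* A patient deteriorates, is removed under (4), or under (1) after four missed sessions, and is operated on later but by day 30. Nothing in the text says this operation would be observed.
- *Operation before removal.* A patient is operated on, misses four sessions and is removed. The event has occurred and may be on file. It is lost only if removal also takes the patient out of the comparison.

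**4. Comparison of the arms.**

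| Criterion | Acupuncture | Control |
|---|---|---|
| (1) missed sessions | applies | cannot apply |
| (3) severe adverse events | applies | applies |
| (4) deterioration | applies | applies |
| (5) decompensation from other disease | applies | applies |
| (6) investigator's judgement | applies | applies |

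Only operated acupuncture patients removed under (1), and who would not have been removed under (3) to (6), create an imbalance. Criterion (4), applied equally, lowers the event count in both arms and favours neither.

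**5. How the sample size treats non-adherers.** Inputs from Sample size calculation: SD 4.2, difference 2.3, power 80%, α = 0.05; two-sided from Statistical analysis.

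n per group = 2 × (1.960 + 0.842)² × 4.2² / 2.3² = 52.3, so 53.

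Inflated for 10% + 3%: 53 / 0.87 = 60.9, so 61; 61 × 8 = 488. The stated total is reproduced exactly. Taking the two losses in sequence, 53 / (0.90 × 0.97) = 60.7, also gives 61.

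Had the 10% been kept in their arm and allowed for as dilution, assuming no benefit in them, the figure would be about 53 / (0.90² × 0.97) = 67.5, so 68. The calculation thus handles non-adherent patients like patients lost to follow-up. This supports the reading that they contribute no data, but does not prove it.

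**6. Rough scale of removals.** 10% of 61 is about 6 patients per acupuncture group, and 10% of 244 (= 488/2) is about 24 in the arm. The article does not define non-adherence as more than three missed sessions, so this is only an order of magnitude. How many of these patients would have been operated on is not given.

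**The case against.** The strongest reply concerns timing. Under criterion (1) the operation will usually come first and the missed sessions after it. The trial runs in one neurosurgical unit, and Safety evaluation has adverse events recorded on case report forms whatever the intervention. An operation before removal is therefore likely to be on file, and bias arises only if it is later dropped. For an operation on day 30 the window has already closed, so later missed sessions matter only if a recorded outcome is erased. This stands, and it makes the concern conditional. It does not cover operations after removal, and the article does not say that events before removal count in this outcome.

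Second, the arms are less unequal than criterion (1) suggests. Many operated patients could be removed in either arm under (3) to (6). Treatment is given at the bedside according to the STRICTA table, so some operated patients may miss few sessions. Both points stand; only the excess matters.

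Third, a reader might infer several stronger claims that the document does not support:
- That a particular spurious reduction in surgery, or a particular false-positive rate, follows. Any such figure needs a surgery rate and a removal fraction that the article does not give.
- That criterion (4) by itself favours acupuncture. It applies to both arms, and only to deterioration that makes continuing difficult, not to every deteriorating patient.
- That removed patients' earlier data will be discarded. The text says they are removed, not that their data are deleted.
- That the endpoint definition is wrong. It agrees with the Abstract, and replacing it with any neurosurgical operation would be a matter of preference.

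**Conclusion.** The concern holds in a limited form. The protocol article states a removal rule that overlaps the 30-day surgery event in both arms and, through criterion (1), reaches further in the acupuncture arm only. If removed patients leave the comparison, events can be lost unequally, in the direction that favours acupuncture.

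The conclusion rests on two assumptions: that removal from the study takes the patient, or later follow-up, out of the comparison, and that some deteriorating or operated acupuncture patients miss four or more sessions without also meeting (3) to (6). If events before removal are kept and follow-up continues, there is no bias. The size cannot be derived from the document. The point is minor: it is confined here to one secondary outcome and does not alter the reproduced sample size of 488.

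**What to change.** Reword Dropout criteria so that meeting (1) or (4) stops acupuncture only and does not end participation. Continue follow-up of these patients, subject to consent. Keep the 30-day surgery outcome exactly as defined in Secondary outcome measures, and state that it is counted by randomised arm over all randomised patients, including events before or after a criterion is met.

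The cost is mainly wording. A 30-day assessment is already planned and case report forms already exist in both arms, so no extra patients or procedures are needed for this outcome. The downsides are slightly more follow-up of patients who have stopped treatment and some dilution of any effect from keeping non-adherent patients in the acupuncture arm.

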### Safety evaluation

Any adverse events or abnormalities will be recorded on case report forms no matter what intervention is used. The severity of such adverse events will be described as mild, moderate, or severe, and the relation of the events to the intervention will be evaluated as not related, possibly related, or related. If any serious adverse events occur as the result of a certain intervention, that intervention will be stopped immediately and appropriate corrective action will be taken. Any serious adverse events will be reported promptly to the institutional review board, according to the protocol.

### Sample size calculation

Using the variable NIHSS score, the primary outcome measure of the study, PS Power and Sample Size software (version 3.0) was used to determine an appropriate sample size for the study. In a previous study, NIHSS scores in each subject group exhibited a normal distribution with a standard deviation of 4.2 points [11]. This assumes a difference of 2.3 points between the groups, as shown in a previous study on moderate TH. A sample size of 488 provides 80% power (α = 0.05) to detect a beneficial effect of early acupuncture therapy on the primary outcome, assuming a 10% non-adherence to treatment and a 3% loss to follow-up.

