Acupuncture, one of the major branches of Traditional Chinese Medicine (TCM), has long been used to treat acute stroke, including hemorrhagic stroke, in China as well as in many other East Asian countries. Acupuncture’s utility in the treatment of non-hemorrhagic stroke, which is now documented by the WHO (World Health Organization, 2002), has been widely researched [18]. In recent years, a number of studies using modern technologies have shown that acupuncture may have neuroprotective effects following hemorrhagic stroke as well [19–22]. One preclinical systematic review of 19 animal studies showed that GV20 (Baihui) based acupuncture can improve neurologic outcome by regulating the inflammatory response to a hematoma, inhibiting neuronal apoptosis, reducing cerebral edema, maintaining ATP supply, promoting nerve regeneration, maintaining neuronal membrane integrity, and promoting hematoma resorption [23]. In another animal study, acupuncture at the DU20 acupoint was reported to have a neuroprotective effect on cerebral hemorrhage by inhibiting Notch-Hes signaling in rat basal ganglia [24]. It has also been reported that electro-acupuncture treatment at the Zusanli (ST36) acupoint may accelerate ICH-induced angiogenesis via the up-regulation of the HIF-1α protein and therefore may enhance recovery following hemorrhagic cerebral injury [25]. A separate study confirmed that treatment at the ST36 acupoint may aid recovery following central nervous system intracerebral hemorrhage in rats [26]. Although animal studies have led to progress in determining how acupuncture exerts its benefits in the treatment of acute hemorrhagic stroke, the determination of its clinical value remains incompletely assessed [27–30].

To our knowledge, no organized study has reported on the effects of acupuncture in patients with acute moderate TH. Specifically, no prior study has examined whether or not the use of acupuncture combined with conventional treatments improves the prognosis of moderate TH patients compared to conventional treatments alone.

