## Methods/Design

### Aims

We hypothesize that the addition of acupuncture to conventional treatments will improve neurological prognosis in TH patients. To test this hypothesis, we will compare study and control groups created based on the size and side of the TH. The study groups will receive acupuncture in addition to standard treatments, while the control groups will receive standard treatments alone.

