### Study design

This study will be a single-center, randomized, placebo-controlled, parallel group, and patient-assessor-blinded clinical trial. After completing informed consent, 488 eligible patients will be recruited and randomized to one of eight groups: 10–15 cc left sided TH study group (*N* = 61) and a corresponding control group (*N* = 61), 10–15 cc right sided TH study group (*N* = 61) and a corresponding control group, 15–30 cc left sided TH study group (*N* = 61) and a corresponding control group (*N* = 61), and 15–30 cc right sided TH study group (*N* = 61) and a corresponding control group. The patients in each of the study groups will receive 36 sessions of Chinese acupuncture in addition to standard treatments for TH, which include anticonvulsant therapy, antihypertensives, osmotic diuretics for the management of intracranial pressure, and invasive treatments as necessary. The patients in each of the control groups will receive standard treatments only. Patients’ neurologic status will be assessed at baseline and at the end of treatment as well as at 30 day and 90 day follow-up intervals. CT imaging will be performed on admission and at 90 days follow up. All patients will be required to complete written informed consent prior to enrollment. If patients are unable to complete written informed consent, it will be obtained from their relatives. A flow chart demonstrating an outline of the study is included in Fig. 1.

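### The 80% power stated for 488 patients is the power of one 61 v 61 size-by-side stratum, and the plan does not say how its four stratum comparisons answer its single hypothesis

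*Protocol article*

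**What the plan says.** All references are to the protocol article.

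- **Sample size calculation.** The calculation starts from "Using the variable NIHSS score, the primary outcome measure of the study". Scores in each subject group of a previous study are said to have "exhibited a normal distribution with a standard deviation of 4.2 points". The next sentence reads "This assumes a difference of 2.3 points between the groups, as shown in a previous study on moderate TH". The conclusion is that "A sample size of 488 provides 80% power" at α = 0.05 for a beneficial effect of acupuncture, allowing for 10% non-adherence and 3% loss to follow-up. The section does not say that this power is per stratum.
- **Study design.** "488 eligible patients will be recruited and randomized to one of eight groups", each of 61: four strata (10–15 cc or 15–30 cc, left or right), each with an acupuncture and a control group.
- **Aims.** One hypothesis is stated, that adding acupuncture improves neurological prognosis in TH patients. To test it, "we will compare study and control groups created based on the size and side of the TH".
- **Statistical analysis.** Two-group tests (Student's t test for continuous data) at two-tailed P < 0.05. No pooled or stratified test and no division of alpha is given.
- **Discussion.** Left- and right-sided hemorrhages are to be examined separately, and the further split by volume makes eight distinct groups.

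**The concern.** The power sentence speaks of one effect, one alpha and the whole trial. The design it describes was sized for something else: one two-arm comparison, repeated in four strata. As written, the sentence gives the wrong power for the 488 and does not tell the reader what the 80% refers to.

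This matters beyond labelling because the primary comparison is left open. One hypothesis is stated, four comparisons are built to test it, and nothing says whether one positive stratum is enough, whether all four are needed, or whether the strata are to be combined. These are different trials, with different false-positive risks and different power. If the choice is made after the results are seen, the data can drive it.

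**Working it through.** **Inputs**

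- SD σ = 4.2, difference δ = 2.3, α = 0.05, power 80%, 10% non-adherence and 3% loss: Sample size calculation.
- Two-sided testing: Statistical analysis. The sample size section does not give the sidedness.
- 1:1 allocation within each size-by-side stratum: Randomization and blinding.
- Eight groups of 61: Study design.

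**1. Reproducing 488**

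n per arm = 2(z₀.₉₇₅ + z₀.₈₀)² σ²/δ² = 2 × (1.960 + 0.8416)² × 4.2²/2.3² = 52.3, rounded up to 53.

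Allowing for loss: 53/(1 − 0.13) = 60.9, or 53/(0.90 × 0.97) = 60.7. Both round up to 61. Then 8 × 61 = 488.

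The figure reproduces exactly, but only as the size of one two-arm comparison (2 × 61 = 122) taken four times. A single overall comparison on the same inputs needs 106 evaluable patients, or 122 after allowing for 13% loss.

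**2. Power of one stratum**

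About 53 v 53 evaluable: 80.5% by the normal approximation, 79.8% by the noncentral t. This is the stated 80%.

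**3. Power of all 488 as one comparison**

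488 less 13% is about 212 v 212. The standardised difference is 2.3/(4.2 × √(2/212)) = 5.64, against 2.3/(4.2 × √(2/53)) = 2.82 in one stratum. Power by the noncentral t is 99.99%.

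The difference detectable with 80% power is 2.80 × 4.2 × √(2/212) = 1.14 points (1.15 by the noncentral t), about half of 2.3.

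This assumes that the SD of 4.2, which the article gives for each group, also holds across strata. With a pooled SD of 4.7, the power of an unstratified test is 99.89%.

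**4. Four stratum tests, each at two-sided 0.05**

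The strata contain different patients, so the tests are independent.

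| Rule (none is stated in the article) | Consequence |
|---|---|
| Any one positive stratum supports the hypothesis | Familywise error 1 − 0.95⁴ = 18.5% |
| All four strata must be positive | No inflation of error; joint power 0.80⁴ = 41% |
| Bonferroni, 0.05/4 = 0.0125 each | Power 61% per stratum at 53 v 53 |

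The joint power assumes a true difference of 2.3 in every stratum. At 0.0125, 80% power would need 75 evaluable per arm, about 87 enrolled (75/0.87 = 86.2).

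**The case against.** The strongest reply is that nothing has been miscalculated. The total follows exactly from the inputs and the eight-group layout, and the Aims and Discussion point clearly to separate stratum comparisons. On that view the 80% is per stratum by implication, a pooled test on all 488 is not in the plan, and detailed multiplicity rules may sit in an analysis plan that is not shown.

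Much of this stands. A reader might infer an arithmetic error in 488; there is none. A reader might also infer that the trial simply has an 18.5% false-positive risk together with a 41% chance of success. The documents do not support that: the two figures belong to different decision rules, and neither rule is stated. Nor is the pooled test the only sound repair, since the article gives reasons for separating the strata.

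Two further criticisms are tempting and should not be made.

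- **Non-adherence counted as lost sample.** The Dropout criteria remove study-group patients who miss more than three sessions, so the inflation is consistent with the article's own rule.
- **The 2.3-point difference.** The Background says "no organized study has reported on the effects of acupuncture in patients with acute moderate TH", which might seem to contradict it. But the sample size section says "This assumes a difference of 2.3 points between the groups", so it is already labelled an assumption. It is credited to a previous study on moderate TH, not to an acupuncture study.

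What the reply does not answer is the power sentence itself. It attaches 80% to 488 patients and one effect, and no unseen document can make that true on the stated inputs.

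**Conclusion.** The point holds as a wrong statement of power and an undefined primary comparison. On the article's own inputs, 80% is the power of one 61 v 61 stratum. For all patients in one comparison it would be over 99.9%, provided the SD across strata is close to 4.2; a moderately larger SD would not change the conclusion. The article tests one hypothesis through four comparisons at 0.05 without saying how they combine. Depending on the rule, that means up to 18.5% familywise error or about 41% joint power. Both figures are conditional on their rule, and both count only the four strata.

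**What to change.** Restate the power sentence and name the primary comparison before analysis. Either of two repairs is sound.

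- **(a) One primary test.** Compare acupuncture with control in all 488 (244 v 244), stratified by side and volume. State its true power: over 99.9% for 2.3 points after 13% loss if the SD is 4.2, or 80% for about 1.15 points. Report the four stratum effects and a treatment-by-stratum interaction test as secondary.
- **(b) Four primary tests.** Label the 80% as the power of each stratum at unadjusted 0.05. Add a rule for alpha across the four strata and give the resulting power, for example about 61% each under Bonferroni.

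The cost is a rewording of the sample size and analysis paragraphs, with no extra patients. The downside is that under (a) the stratum-specific claims become secondary, and under (b) the stated power per stratum becomes less favourable.

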## Background

Spontaneous intracerebral hemorrhage (ICH), non-iatrogenic ICH without trauma, is the second most common and the most devastating form of all strokes with the poorest prognosis [1, 2]. Approximately 15% of all cases of spontaneous ICH occur in the thalamus [3–5]. The thalamus is a deep brain structure and is an important center for the transmission of neural signals [3, 6]. Due to its anatomical location and the vital functions that it performs, the decision of conservative or surgical management for TH remains controversial [2, 7, 8]. Management is influenced mainly by the clinical experience of the treating surgeon and the volume of the hematoma [9]. Patients with minor TH, especially volumes less than 10 cc, usually obtain favorable outcomes when treated with conservative measures. However, patients with major TH, greater than 30 cc, have mortality rates of more than 80%, no matter what treatment is selected [10]. Moderate TH (10–30 mL) constitutes more than half of all cases of TH, and these patients have a mortality rate of more than 30% [11]. As moderate TH is the most common form of TH, its prognosis carries the greatest weight in calculating the prognosis of all forms of TH. In patients with moderate TH, conservative treatment alone versus surgical treatment is naturally a difficult decision to make. Because surgical treatment is invasive, adjacent structures may be damaged and neural pathways may be disrupted during surgical evacuation of a hematoma, thereby aggravating the degree of neurologic deficits or creating new ones. Meanwhile, conservative treatment alone does not offer the involved thalamic tissue the same type of relief that evacuation offers and is therefore felt to be a limited strategy in improving neurologic function. The limitations of both therapeutic strategies provide considerable room for better approaches or combinations of approaches.

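### The sample size makes no allowance for death, although the protocol puts mortality of moderate TH above 30% and NIHSS has no value for a dead patient; the stated 80% power per size-and-side pair is overstated if deaths go unscored

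*Protocol article*

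**What the plan says.** - **Mortality.** The Background of the protocol article says of moderate TH (10 to 30 mL), the trial's population by volume, that "these patients have a mortality rate of more than 30" per cent. It gives no time horizon. The reference cited is the one from which the sample size section takes its SD of 4.2.
- **Primary outcome.** NIHSS is measured at the end of treatment, at 30 days and at 90 days. The scale is described thus: "Total score ranges from 0 to 42, with scores above 25 indicating very severe neurological impairment". No value is assigned to death.
- **Secondary outcomes.** Death has a place here: "Poor outcome, defined as death or major disability, is defined as a score of 3 to 6 on the modified Rankin scale", with 6 meaning death, and grade 1 of the GOS is death.
- **Sample size.** The effect is put as follows: "This assumes a difference of 2.3 points between the groups, as shown in a previous study on moderate TH". The total of 488 is then said to give 80% power at an alpha of 0.05 for the primary outcome. The only allowance for attrition reads: "assuming a 10% non-adherence to treatment and a 3% loss to follow-up".
- **Comparison and test.** The Aims compare study and control groups formed by size and side of the hemorrhage. The Statistical analysis section gives the t test for continuous data and the Mann-Whitney test for multi-ranked data, at a two-sided 0.05 level. It does not name the test for NIHSS.
- **Removals.** The Dropout criteria also take out patients whose neurological state worsens or who have severe adverse events that make their further inclusion unsustainable.

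**The concern.** The attrition assumption and the mortality figure do not fit together. At 30% mortality, 0.30 x 488 = about 146 patients would die. The plan allows for 0.03 x 488 = about 15 lost to follow-up, or 0.13 x 488 = about 63 if every non-adherent patient is also counted as lost.

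Two things are at stake. The first is the stated power, if patients who die contribute no NIHSS value. The second is what the primary comparison means. Survival to 90 days happens after randomisation and may depend on treatment. If acupuncture kept more severe patients alive, their high scores would enter only its arm and count against it; if more of them died under acupuncture, its arm would look better. A larger sample does not remove this.

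**Working it through.** **Inputs.** Difference 2.3, SD 4.2, power 80%, 10% non-adherence and 3% loss (Sample size calculation); two-sided alpha 0.05 (Statistical analysis); eight groups of 61, that is four pairs (Study design); mortality above 30% (Background).

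**Step 1: reproduce 488.** The number per group for two means is n = 2(1.960 + 0.842)² x 4.2² / 2.3² = 52.3, so 53. Inflated for the 13% allowance: 53 / 0.87 = 60.9, so 61. Then 8 x 61 = 488. The figure reproduces, but only as a calculation for each size-and-side pair. Read as one comparison of 244 v 244, the same inputs give power above 99.9%, not 80%. With 61 x 0.87 = 53.1 per group, power from the exact (noncentral) t distribution is 79.8%.

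**Step 2: remove deaths.** Assume that patients who die have no NIHSS, that mortality m is equal in both arms, and that death is independent of the other losses. The number analysed per group is 61 x (1 - loss) x (1 - m). The noncentrality is 2.3 / (4.2 x √(2/n)); at n = 37.1 it is 2.36. Exact-t power per pair:

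| Mortality | n, 13% loss | Power | n, 3% loss | Power |
|---|---|---|---|---|
| 10% | 47.8 | 75% | 53.2 | 80% |
| 20% | 42.5 | 70% | 47.3 | 75% |
| 30% | 37.1 | 64% | 41.4 | 69% |
| 40% | 31.8 | 58% | 35.5 | 62% |

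The 13% columns treat every non-adherent patient as having no outcome. The 3% columns keep non-adherers in the analysis with no dilution of the effect. With the full 13% lost, the plan is already at 80% with no deaths, so any mortality takes it below. With 3% lost, power falls below 80% once mortality passes about 10%.

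**Step 3: pooled over the four strata.** At 30% mortality and 13% loss, 4 x 37.1 = 148.6 per arm remain, and power is 99.7%.

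**Step 4: would scoring deaths as 42 in a t test restore the power?** The protocol does not propose this. The SD becomes √[(1 - m) x 4.2² + m(1 - m)(42 - μ)²], where μ is the survivors' mean, which the protocol does not give. For assumed μ from 5 to 20 and m = 0.30, the SD is about 17.3 down to 10.7. Power per pair for a 2.3-point difference is then about 10% to 22%. It would not.

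**Step 5: death ranked worst.** This is a simulated rank test with 53 per arm per stratum, 30% deaths in both arms, and a shift of 2.3 with SD 4.2 in survivors. Power is about 25% per pair. The stratified (van Elteren) test over four strata has about 75%. The like-for-like figures for the t test in survivors are 64% and 99.7% (13% loss). Ranking death worst therefore costs power when mortality is equal in the two arms.

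**The case against.** Four points can be made for the plan.

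1. *The protocol nowhere says that deaths are left out of the NIHSS analysis.* This stands. A reader might infer that the plan is a survivors-only t test at 90 days. The document does not say so: it names three time points, does not assign a test to NIHSS, and leaves the handling of deaths to be stated elsewhere, possibly in an analysis plan not shown. The survivor problem is therefore conditional. An analysis plan could add a rule for deaths, but it would not reconcile the printed attrition figures with the printed mortality.

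2. *30% need not be the trial's mortality.* This stands as well. The figure is for moderate TH in general. The trial excludes age over 70, extension beyond the thalamus, continued bleeding, other lesions, and heart, liver or renal failure. A reader might take 64% as the trial's power. It is the result at 30% mortality with every non-adherent patient lost. At 10% mortality and 3% loss there is practically no shortfall. But the protocol states no lower mortality.

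3. *Pooling removes the power problem.* Correct, so a reader would be wrong to infer that the trial as a whole is underpowered. But 80% is the power of a pair, and pairs are what the Aims compare. Pooling also does not change who is compared if deaths are left out.

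4. *Death is already covered by the modified Rankin scale and the GOS.* True, and a reason not to insist on a new primary outcome. A composite with death ranked worst mixes death and deficit, answers a different question, and costs power (step 5). The documents do not show that it must replace NIHSS.

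**Conclusion.** The point holds as an inconsistency within the protocol article. Its sample size makes no allowance for death, for an outcome with no value for death, in a condition to which its own Background gives a mortality above 30%. If deaths have no NIHSS, the 80% per pair becomes about 64% to 69% at 30% mortality, 70% to 75% at 20% and 75% to 80% at 10%. This rests on equal mortality in both arms, the plan's own difference and SD, and comparisons within size-and-side pairs. It does not extend to a pooled comparison, where power stays above 99%. That the primary contrast would be confined to survivors follows only if deaths are in fact left out; the text does not settle this, and it should. The size and direction of any resulting bias cannot be computed from the document.

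**What to change.** - **Sample size section.** Reconcile it with the Background: state the mortality expected by 90 days under the eligibility criteria, include it in the attrition assumption, and say whether the 10% non-adherence means missing outcomes. Restate power per pair as a range, as in the table above. This correction needs no larger enrolment.
- **Primary outcome and analysis.** State how patients who die enter the NIHSS analysis at each time point.
- **Reporting.** Give mortality by arm beside NIHSS in survivors.
- **Sensitivity analysis.** Add a stratified rank analysis in all randomised patients, with death ranked worse than any living score.

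**Cost.** Changes of text only, with no new data, because death is already recorded for the modified Rankin scale and the GOS. The stated power becomes less favourable. The rank analysis has low power if mortality is equal (about 25% per pair and 75% pooled at 30% mortality, with 53 per arm per stratum), so it should support the primary outcome and need not replace it.
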